### 2.6. Blinding

Due to the study design, the treating clinician cannot be blinded to group allocation. However, the outcome assessor will remain blinded to group allocation throughout the study period to maintain objectivity in data collection and analysis.

To minimize the risk of assessor unblinding, the assessor will not be present in the clinical setting during intervention delivery, and the clinician will remind participants not to disclose their assigned intervention during outcome assessments. Although the invasive nature of PENS may pose a theoretical risk, these procedures are expected to maintain assessor blinding throughout data collection.

To formally evaluate blinding integrity, the assessor will be asked at each outcome assessment (A2: immediately post-intervention; A3: 24 h post-intervention; and A4: 7 days post-intervention) to guess each participant’s group allocation and provide a confidence in this judgment. This procedure will allow monitoring of blinding effectiveness, particularly given that participant and treating clinician blinding is not feasible.

### 2.7. Interventions

The trial will comprise three groups: the control group (conventional post-ACLR rehabilitation program (CRP) only), the TENS group (CRP plus a single high-frequency TENS session), and the PENS group (CRP plus a single LTP PENS session).

The primary objective of this study is to evaluate the added efficacy of TENS or PENS when combined with CRP, rather than comparing these interventions against a placebo. The implementation of a sham intervention for TENS or PENS is inherently challenging because the sensory characteristics of both procedures make it difficult to create a fully convincing placebo. For TENS, the perception of electrical stimulation is readily apparent to participants, while for PENS, no sham needles are available.

To minimize the potential influence of performance and placebo-related effects, se-veral strategies will be implemented. Outcome assessors will remain blinded to group allocation. All participants will receive standardized instructions and procedures. Participants will be instructed not to reveal their assigned treatment to the assessor. The same CRP will be applied consistently across all groups. These measures aim to reduce expectancy bias and its impact on objective outcomes, such as pressure pain threshold and QMVIC.

All participants will perform CRP according to the graft ligamentization phase [21]. CRP will include passive knee mobilization (30 min) using a continuous passive motion device (Artromot^®^-K1, Chattanooga, Barcelona, Spain), manual therapy (≤15 min), and therapeutic exercise. Manual therapy will consist of passive knee joint mobilizations, drainage of the suprapatellar recess, surgical scar massage and myofascial soft tissue techniques. Therapeutic exercise will consist of 3 sets of 10 repetitions with 1 min rest intervals and will include the following exercises: abdominal crunches, supine, prone, and side-lying straight leg raises, inner thigh squeezes, isometric knee extensions, isometric seated hamstring curls, and calf raises [23]. Photographic examples of these exercises are provided in Figure 1.

Participants will perform the exercises at the same workload used prior to study initiation. The rehabilitation program was standardized and identical for all participants across groups, with no additional progression or load modification during the study.

All interventions will be delivered by the same experienced clinician specialized in invasive physiotherapy techniques. The Duo Tens Globus^®^ electrostimulator (Fisiomundo Tecnología Médica y Rehabilitación SL, Alicante, Spain) will be used to deliver a biphasic, symmetrical, square waveform current to the targeted motor points [45,60].

Once participants provide written informed consent, the blinded assessor will perform the baseline assessment (A1). Immediately afterward, the assessor will leave the clinical setting, and the clinician, if applicable, will administer a single 30 min TENS session or a single 5 min LTP PENS session. The clinician will also instruct all participants on the guidelines for performing the CRP over the following 7 days, which will constitute the total duration of the program. Table 1 summarizes the key characteristics of the interventions applied in each study group, highlighting the differences between the control group, the TENS group, and the PENS group.

Control Group: Participants will perform CRP only.

TENS Group: During the sixth postoperative week, participants will perform CRP and receive a single high-frequency TENS session. Two surface electrodes (5 × 5 cm) will be placed over the distal zone of the middle third of the vastus medialis and distal zone of the proximal third of the vastus lateralis [61,62]. Stimulation parameters will be 100 Hz frequency, 200 μs pulse width, intensity adjusted to each participants’ pain threshold, and duration 30 min. Participants will be allowed to adjust intensity during the session.

The TENS protocol specifies a reproducible criterion for adjusting intensity by increasing pulse amplitude to achieve a strong but comfortable sensation [60], tailored to each participant’s tolerance threshold and consistent with the scientific literature [30,32,63,64]. Moreover, evidence suggests that higher intensities produce greater effects and may prevent analgesic tolerance [30,32,63,65].

No predefined intensity algorithm will be used; however, the clinician provides consistent instructions for all participants in the TENS group to adjust stimulation according to their individual pain threshold during administration, ensuring standardized delivery.

When the high-frequency TENS session begins, the clinician will progressively increase stimulation intensity until the participant reports a strong but comfortable sensation [60]. To ensure reproducibility and transparent reporting of the delivered dose, the final stimulation intensity will be recorded for each session. The device allows a maximum output of 100 mA, and a standardized patient-reported perceived intensity rating (0–10 scale) will be recorded at session end. Only the final intensity will be reported, as no other parameters are adjusted during application. Stimulation intensity data will be reported descriptively to characterize the delivered dose.

PENS Group: During the sixth postoperative week, participants will perform CRP and receive a single long-term potentiation PENS session. Motor points will be identified according to Page et al. [62] and the needle puncture will be performed following the guidelines described by Velázquez-Saornil et al. [66]. A sterile acupuncture needle (0.30 × 40 mm, Tony^®^, Calvo Izquierdo S.L., Requena, Spain) will be inserted into the vastus medialis motor point. The knee will be passively flexed to 30°, and the skin will be disinfected with chlorhexidine. If the needle contacts the femoral cortex, it will be slightly withdrawn to avoid periosteal stimulation [60,67,68]. An electrode (5 × 5 cm) will be placed on the anteromedial knee to cover the infrapatellar branch of the saphenous nerve and medial femoral cutaneous nerves [69,70]. Electrical stimulation will be delivered at 100 Hz, 250 μs pulse width, at a perceptible but not painful intensity (200 μA above detection threshold), in five 5 s bursts with 55 s rest intervals [45].

Hemostasis will be performed for 60 s after needle withdrawal [45].

No adverse effects are expected due to the anatomical location of the puncture and the minimally invasive nature of the procedure. The puncture will be performed cranial to the suprapatellar recess and lateral to the sartorius muscle, posing no risk of intra-articular infection and avoiding the saphenous nerve in Hunter’s canal [71,72,73]. The intervention will be delivered by a qualified physical therapist with expertise in invasive approaches. All procedures will be conducted in the clinical setting of the Clínica CEMTRO, following standardized procedures [62,66].

In the unlikely event of an unexpected adverse reaction, the invasive intervention will be halted, and the adverse-event (AE) monitoring plan will be implemented, which will vary depending on the specific AE. Expected AEs for PENS include bleeding/bruising, neuropathic symptoms, vasovagal responses and infection signs.

The clinician delivering the intervention will collect all AE data immediately post-needling (A2) and at each follow-up assessment (24 h and 7 days post-intervention, A3 and A4, respectively). All AEs will be documented using a standardized form noting severity (mild/moderate/severe). Mild or moderate events will be managed in the clinical setting, while severe or unexpected events will be referred to hospital services for appropriate care.

As only non-anticoagulated participants are recruited [53], hemostasis for 60 s after needle withdrawal will address bleeding and bruising. If bleeding persists beyond 60 s, hemostasis will be continued until complete cessation. If the participant reports minimal neuropathic symptoms, the clinician will adjust the needle angulation until symptoms resolve. If this is insufficient, the clinician will repeat the puncture procedure.

In the presence of objective signs or subjective reports of a vasovagal response, the participant will be placed in a fully supine position. Legs will be elevated to promote venous return and to help maintain stable cerebral perfusion. If the participant reports a sensation of heat, the room environment will be adjusted by opening a window to reduce temperature and improve oxygen availability.

Although strict aseptic techniques will be applied as a preventive measure for infection, participants will be referred to hospital services for appropriate care should any signs of infection occur.

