### 2.8. Outcomes

Assessments will be conducted at four time points: pre-treatment (A1), immediately post-treatment (A2), 24 h post-treatment (A3), and 7 days post-treatment (A4). All assessments will be conducted by an assessor blinded to group allocation and will be performed in the same clinical setting at Clínica CEMTRO (Madrid, Spain), under standardized conditions. The order of outcome assessment will be identical whenever applicable. All outcomes will be assessed according to the schedule presented in Table 2.

Baseline descriptive variables will include sex, age, body mass, height, BMI, limb dominance, operated limb, graft type (hamstring tendon autografts, bone–patellar tendon–bone autografts, quadriceps tendon autografts or allografts), associated lateral extra-articular tenodesis, and meniscal procedures (none, repair, debridement, rasping, partial meniscectomy). Surgery-related sensory disturbances (none, anesthesia, hypoesthesia, hyperesthesia, paresthesia) will also be recorded.

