#### 2.8.1. Primary Outcome

Quadriceps maximal voluntary isometric contraction (QMVIC) of the operated limb will be measured using a calibrated hand-held dynamometer (Lafayette Manual Muscle Tester, Lafayette Instruments, Lafayette, IN, USA), which has demonstrated excellent intra-rater reliability [ICC = 0.98; 95% CI, 0.98–0.99] [74]. All measurements will be performed by an assessor experienced in hand-held dynamometry in previous research studies.

Participants will be seated with an upright trunk, 90° hip flexion, and 75° knee flexion [75,76]—a position associated with minimal stress on the ACL graft [77]. Thigh stabilization will be applied to prevent compensatory movements, and participants will be instructed to hold the edge of the treatment table if needed [75,78]. To ensure measurement validity, knee angle will be set using a 360° universal manual goniometer prior to each QMVIC assessment, following the guidelines of Norkin [79]. The dynamometer will be aligned with the lateral femoral condyle, and resistance will be applied to the anterior tibia 2 cm proximal to the malleoli [41,80].

Three maximal contractions of 5 s each will be performed, with 60 s of rest between trials. Standardized verbal encouragement will be provided during each contraction. The highest absolute force value (N) will be recorded [75,76,78,81]. Torque values will not be normalized to body mass or lever arm.

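### A2 follows the end of treatment with no common A1–A2 interval, so elapsed time can reveal the TENS arm to the blinded assessor and recovery time before A2 differs by arm

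*Protocol article*

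**What the plan says.** Section 2.7 (Interventions) gives the order of events. The assessor does the baseline assessment and leaves straight away; then "the clinician, if applicable, will administer a single 30 min TENS session or a single 5 min LTP PENS session". The control arm has no session: "Control Group: Participants will perform CRP only". One activity after A1 is shared by all arms, and its length is not given: "The clinician will also instruct all participants on the guidelines for performing the CRP over the following 7 days".

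Section 2.8 (Outcomes) sets the assessments at "pre-treatment (A1), immediately post-treatment (A2), 24 h post-treatment (A3), and 7 days post-treatment (A4". A2 is therefore tied to the end of treatment, not to a clock time after A1.

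Section 2.6 (Blinding) lists the safeguards: the assessor is away during delivery, participants are reminded not to disclose their arm, and the assessor records a guess of allocation with a confidence rating at A2, A3 and A4. It concludes that "these procedures are expected to maintain assessor blinding throughout data collection". Elapsed time is not mentioned.

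The primary outcome is taken at A1 and again at A2 (section 2.8.1): "Three maximal contractions of 5 s each will be performed, with 60 s of rest between trials".

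**The concern.** Session length is fixed by arm, and the assessor knows both when A1 ended and when A2 begins. If A2 starts as soon as treatment ends, the length of the wait carries information about the arm. The safeguard of sending the assessor away does not remove that information; it makes the wait the thing the assessor observes.

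Two things are at stake.

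- **Masking.** Participants and the clinician are unblinded, so the assessor is the only blinded party. This person takes the primary outcome with a hand-held dynamometer, and verbal encouragement, although standardised, accompanies each contraction.
- **Comparability at A2.** The interval since the A1 maximal contractions and repeated algometry differs by arm. Because it is set by arm, no covariate adjustment can separate it from treatment. The Introduction says the single session was chosen to test an acute effect, so A2 is not a peripheral time point.

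**Working it through.** **Inputs from the protocol**

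- TENS session: 30 min (section 2.7, Table 1).
- PENS session: 5 min (section 2.7, Table 1), delivered "in five 5 s bursts with 55 s rest intervals".
- After PENS: "Hemostasis will be performed for 60 s after needle withdrawal".
- Control: no session.
- X: time common to all arms between A1 and A2 (CRP instruction, possibly CRP itself). Not stated.
- Arm-specific set-up time (electrode placement, landmarking, disinfection, finding the intensity): not stated, set to zero below.

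**Step 1. Reproduce the plan's PENS duration.**
5 × (5 s + 55 s) = 300 s = 5 min, which matches the stated figure. Without the final rest it is 5 × 5 + 4 × 55 = 245 s. With the 60 s of hemostasis it is 300 + 60 = 360 s = 6 min.

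**Step 2. A1–A2 gap by arm.** Gap = session length + X.

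| Arm | Gap | X = 0 | X = 45 min |
|---|---|---|---|
| TENS | 30 + X | 30 | 75 |
| PENS (with hemostasis) | 6 + X | 6 | 51 |
| Control | X | 0 | 45 |

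X = 45 min is an illustration: 30 min of passive motion plus the maximum 15 min of manual therapy from section 2.7, as if both were done in this window. The protocol does not say that they are.

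**Step 3. Differences, in which X cancels.**

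- TENS − PENS: 30 − 6 = 24 min, or 30 − 5 = 25 min without hemostasis.
- TENS − control: 30 min.
- PENS − control: 5 to 6 min.

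If PENS set-up takes s min longer than TENS set-up, the first difference falls to about 24 − s. It would vanish only if PENS set-up ran some 24 min longer.

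**Step 4. What the delay is worth to an assessor guessing the arm (18 per arm, 54 in all).**

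- Chance: 18/54 = 33%.
- TENS recognised, PENS and control guessed at random: (18 + 36 × 0.5)/54 = 36/54 = 67%.
- All three recognised: 54/54 = 100%. This needs PENS and control to be separable on 5 to 6 min plus unstated set-up.

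**Step 5. Recovery time.** Section 2.8 keeps the assessment order the same where applicable. The time from the A1 strength test to the A2 strength test is then the length of the assessment battery plus the gap, and the Step 3 differences carry over in full. The load to recover from is 3 × 5 = 15 s of maximal effort and 6 sites × 3 = 18 algometry readings. Nothing in the document converts a difference of 24 to 30 min into newtons or kg/cm², so the bias cannot be sized, and its direction is not known either.

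**Step 6. With one fixed interval in all arms.** The between-arm difference in gap is 0 min and the delay carries no information on allocation.

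**The case against.** The strongest reply has four parts.

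1. **The control gap is not stated.** A reader might infer that controls go from A1 to A2 with no gap at all. The text does not say so: CRP instruction of unknown length comes after A1, a CRP session might too, and the timeline in Figure 2 is not available here. A condensed article may also leave visit clock times to the full protocol. This stands as to the control value, which is undefined. It does not remove the TENS–PENS difference, which follows from the sequence the article itself states.

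2. **The rest-time effect may be trivial.** The protocol treats 60 s as enough rest between maximal trials, and the A1 effort totals 15 s. The pressure readings alone put 6 sites × 2 intervals × 30 s = 6 min of pauses into each assessment. Every arm may therefore be well rested before the A2 strength test. This largely stands. A reader might conclude that the A2 comparison is dominated by rest time; the documents do not support that.

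3. **Recognition is limited.** PENS and control differ by only 5 to 6 min plus set-up, against a shared period of unknown length. A reader might infer that the assessor can name every arm, but only TENS is clearly separable, and even that assumes the assessor attends to the delay. This stands.

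4. **The risk is partly handled.** Section 2.6 acknowledges a threat to blinding from PENS and records the assessor's guesses. Other protections exist: independent sequence generation, sealed opaque envelopes opened after baseline, standardised instructions and encouragement, and intention-to-treat analysis. It would be wrong to call assessor masking the trial's sole defence against bias; it is the sole blinding. But recording guesses detects unblinding and does not prevent it, and none of the listed measures deals with elapsed time.

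**Conclusion.** The point holds in a limited form. Followed as written, the sequence gives TENS an A1–A2 gap about 24–25 min longer than PENS and about 30 min longer than control. This does not depend on X; it assumes that set-up times do not differ enough to offset it and that Figure 2 fixes no common clock time. An assessor who notices the delay can pick out TENS, which puts correct guesses at up to about 67% against 33% by chance. A higher figure requires PENS and control to be separable as well, which the document does not establish. The expectation in section 2.6 that blinding will be maintained is therefore not supported by the safeguards listed there.

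Recovery time also differs by arm at A2, for strength, pain intensity and pressure pain threshold. That bias is unsized and may be small. A3 and A4 are affected only if a belief formed at A2 carries forward. This is a cheap improvement to make before data collection, not a flaw that invalidates the trial.

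**What to change.** State in sections 2.7 and 2.8 that A2 starts at one fixed interval after the end of A1 in all three arms, long enough for the longest session plus set-up. Place the waiting time before the PENS session, so that A2 still follows treatment directly, and give controls a rest period of the same total length. Any CRP instruction or activity within the window should be identical across arms. Have the assessor return at the fixed time, not when called. Add the fixed interval to the safeguards in section 2.6.

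The cost is about 30 min of extra waiting for control and PENS participants on one day. No stimulation parameter changes and no additional assessor is needed.

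Covering the treated skin with opaque dressings is not recommended as part of this change. Dressings could interfere with the pressure pain sites, the tape measurements and the effusion tests.

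### The A2 adverse-event collection is worded for needling, which only the PENS arm receives, and the text contradicts itself on which events are expected, the term that triggers halting and hospital referral

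*Protocol article*

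**What the plan says.** All the adverse-event text is in section 2.7 (Interventions) of the protocol article, where it follows on from the description of the PENS group.

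- **Who collects, and when:** the treating clinician "will collect all AE data immediately post-needling (A2") and again at the follow-up assessments, which are given as "24 h and 7 days post-intervention, A3 and A4, respectively".
- **How events are recorded:** "All AEs will be documented using a standardized form noting severity (mild/moderate/severe"). No arm is named or excluded.
- **What is expected, first statement:** "No adverse effects are expected due to the anatomical location of the puncture" and its minimally invasive nature.
- **What is expected, second statement:** "Expected AEs for PENS include bleeding/bruising, neuropathic symptoms, vasovagal responses and infection signs".
- **Halting:** the invasive intervention stops if an unexpected adverse reaction occurs.
- **Clinic or hospital:** mild and moderate events stay in the clinic, while "severe or unexpected events will be referred to hospital services for appropriate care".
- **Event-specific handling:** separate instructions follow for bleeding or bruising, minimal neuropathic symptoms, vasovagal responses and infection. The last sends the participant to hospital services for any sign of infection.

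Section 2.8 (Outcomes) sets the post-baseline assessments for all participants as "immediately post-treatment (A2), 24 h post-treatment (A3), and 7 days post-treatment (A4"). Table 2 has one schedule for the whole trial.

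**The concern.** Two things in this text can go wrong in use.

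First, the A2 collection is anchored to a procedure that two of the three arms do not undergo. A clinician who follows the sentence word for word asks PENS participants about adverse events straight after the session and has no matching instruction for TENS or control. Any immediate events later described by arm would then partly reflect who was asked. The clinician who collects the events also knows the allocation, so uniform wording matters more here than it would with a blinded collector.

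Second, whether an event counts as expected is not a descriptive label in this protocol. It decides whether the invasive intervention is halted and whether the participant is referred. If the text gives two answers on what is expected, the safety response can differ between two participants with the same event.

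**Working it through.** No sample-size, power or event figure enters this point, so the check sets the sentences side by side. The only numbers are the arm sizes in section 2.3: 18 per group, 54 in total.

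**1. The A2 collection point**

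- Section 2.7 ties the A2 adverse-event collection to needling. Table 1 shows needle insertion only in the PENS column.
- Section 2.8 defines A2 by treatment, for everyone. One time point therefore has two labels, and the adverse-event sentence uses the one that fits a single arm.
- Participants in arms without needling: 18 + 18 = 36 of 54.
- A3 and A4 are described as post-intervention, with no mention of needling. The wording problem therefore covers one of three collection points.

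**2. What counts as expected**

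Take a mild bruise after PENS, an event on the list:

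| Sentence followed | Status of the bruise | Consequence under section 2.7 |
|---|---|---|
| No adverse effects expected | Unexpected | Halt rule and referral rule both apply |
| List of expected events for PENS | Expected, mild | Managed at the clinic; halt rule not triggered |

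The same event leads to two different responses.

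**3. The clinic-or-referral sentence**

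Its first half sorts by severity (mild or moderate). Its second half sorts by severity or expectedness (severe or unexpected). The two halves overlap: an event that is mild and unexpected satisfies both, so it is assigned to the clinic and to the hospital at once. This holds whichever statement in step 2 is adopted.

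**4. Infection signs**

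They are on the expected list. Under the general severity rule, a mild sign would stay at the clinic. The infection-specific sentence refers any sign to hospital, whatever its severity. The text does not say that the specific sentence overrides the general one.

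**The case against.** The strongest reply is that the adverse-event text is inclusive in substance. It speaks of all adverse events and one standardized form, excludes no arm, and is not tied to needling at A3 or A4. A2 is a common visit, and section 2.7 has the same clinician instruct every participant. The needling wording may simply carry over from the PENS description in which it sits. This stands to the extent that a reader might infer that harms cannot be compared across the arms, and the document does not support that. What remains is that the A2 sentence does not secure identical collection.

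Other stronger readings also fail:

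- **No event list for TENS or control.** This is an omission in a condensed article; the full protocol may contain such a list. It is not a finding.
- **Neuropathic symptoms.** It is tempting to see a clash between needle adjustment or repeat puncture and the halt rule. But the handling sentence concerns minimal symptoms, the halt rule concerns unexpected reactions, and neuropathic symptoms are on the expected list. The clash arises only if the statement that nothing is expected governs.
- **Infection.** Section 2.7 says that the plan varies by event, so the infection sentence can fairly be read as a specific rule over a general one. This calls for explicit wording and is not a firm contradiction.
- **Small numbers.** Zero events in 18 PENS participants would leave a 95% upper limit of 1 − 0.05^(1/18) = 15.3% (one-sided) or 1 − 0.025^(1/18) = 18.5% (two-sided). This describes imprecision in the PENS rate. A comparator would not narrow it, so it does not show that a comparator is needed. Nor does the article state a between-arm analysis of harms.

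It can also be argued that the first expectation statement means only that problems are unlikely at this puncture site. That is a plausible intention, but the halt and referral rules turn on the word itself, so the inconsistency has practical effect.

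**Conclusion.** The point holds in a limited form.

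- **Ascertainment at A2.** Read literally, the instruction covers PENS only and leaves 36 of 54 participants without a matching one. The effect is a risk of unequal ascertainment at one of three collection points. Its size in events cannot be derived from the document. It rests on staff following the sentence as written; if they already treat A2 as a common post-treatment visit for adverse events, the risk disappears in practice.
- **Expectedness.** The two statements in section 2.7 contradict each other, and the response to a listed mild event depends on which is followed. The overlap for mild but unexpected events exists under either statement. The general severity rule and the infection sentence need to be made explicitly consistent.

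The primary outcome, randomization, sample size and efficacy analysis are untouched. The point concerns the consistency of safety handling and the comparability of immediate adverse-event records.

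**What to change.** In section 2.7, state that adverse events are collected at A2 (post-treatment), A3 and A4 in all three groups, with the same standardized form and the same questions.

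Reconcile the two statements on which events are expected. Then reconcile the halting, clinic-management and referral sentences, including the infection sentence, so that each event leads to one response and no event falls under two. Which statement prevails and which response applies is for the investigators to decide; this review takes no position on either.

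The cost is a wording amendment and use of the same form in the TENS and control arms at a visit they already attend. No added visits or staff are needed.
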